### Vaginal ultrasound data acquisition

#### Instrument and collection preparation

The SAMSUNG Hera-W10 Doppler Ultrasound Diagnostic System, equipped with an EV3-10B vaginal probe operating at 3.3 MHz, will serve as the instrument for ultrasound data acquisition. Patients will be directed to empty their bladders and adopt the lithotomy position. Subsequently, a disposable condom will be placed over the ultrasound probe, which will be evenly coated with ultrasound gel. The probe will then be gently and slowly inserted into the subject’s vagina, aiming to reach the posterior fornix for scanning and measurements. This vaginal ultrasound examination will be performed by a seasoned gynecological ultrasonographer with over ten years of experience.

#### Ultrasound acquisition patterns and content

*2D ultrasound pattern*. In the two-dimensional grayscale mode, measurements of endometrial thickness, endometrial morphology, and endometrial motion will be conducted. Endometrial thickness will be determined by averaging three measurements of the distance between the anterior and posterior myometrium-endometrium interfaces, taken 1 cm from the endometrial apex. Detailed observation of endometrial echogenicity will be conducted, and the endometrium will be categorized into types A, B, and C based on the Gonen criteria [17]. Endometrial wave motion will be observed and documented for three minutes on the longitudinal midline section of the uterus with the probe stabilized and the patient breathing normally. Endometrial motion is classified into positive wave, negative wave, quiescent wave, bidirectional wave, local peristaltic wave according to the Ljland criteria [18].

In the two-dimensional color mode, with the uterus longitudinally bisected along its midline axis, the subendometrial region is demarcated as extending 3mm beyond the endometrial margin. Utilizing two-dimensional color Doppler flow imaging (CDFI), the perfusion of the endometrium and subendometrial areas will be assessed, classifying the flow patterns into Type I, II, and III according to the Applebaum criteria [7]. Subsequently, the CDFI is employed to delineate the uterine sagittal section, orthogonal to the long axis of the uterine cavity, where blood flow measurements are conducted. The color imaging technique is used to visualize the uterine arteries, with the sampling gate sequentially positioned at the cervix, both sides of the corpus, and the junction of the myometrium and endometrium to obtain stable blood flow spectrograms. Measurements are taken only after a minimum of consecutive stable waveforms are observed. The resultant parameters of uterine arterial blood flow encompass the peak systolic velocity (PSV), end diastolic velocity (EDV), time-averaged maximum velocity (TAMV), time-averaged peak velocity (TAPV), mean pressure gradient (PGmean), systolic/diastolic ratio (S/D), resistivity index (RI), and pulsatility index (PI).

The MV-FlOW^™^ technology employs advanced clutter filters to evaluate low-velocity blood flow signals. To facilitate MV-FlOW^™^ sample acquisition, the sensor is positioned and the imaging adjusted to focus on the endometrium and the uterus, thereby enabling a quantitative assessment of blood perfusion. The Volumetric Index of Microvascularity (VI^MV^) is computed automatically as the ratio of blood-filled pixels to the total number of pixels within the region of Interest (ROI; VI^MV^ = n_blood/n_total). By activating MV-FlOW^™^, the operator achieves optimal visualization of the vascular tree. In this study, the ROI encompasses the entire uterus, and the VI^MV^ is determined by the proportion of endometrial blood flow pixels to the total blood flow pixels within the uterus. The parameters for the MV-Flow on the Hera-W10 system are standardized as follows: Gain at 54; Frame Average set to 8; Output Power at 90; Dynamic Range of 50; Alpha Blending at 70%; Color Map selected as 2; LumiFlow set to 2; Mechanical Index (MI) at 1.3; Thermal Index (TIs) at 0.3; and Depth calibrated to 6 cm.

*3D ultrasound pattern*. Initiating the power Doppler flow imaging mode, the sensitivity is adjusted to a heightened state to observe the branching patterns of endometrial blood flow. Subsequently, the CrystalVue^™^ mode is activated to delineate the endometrial contour, yielding a three-dimensional representation of the uterine endometrium. This process automatically calculates the endometrial volume (EV), the vascularization index (VI), the flow index (FI), and the vascular flow index (VFI).

### Clinical data acquisition

We will systematically compily comprehensive clinical data for RIF or FI patients, encompassing their foundational details such as chief complaints, present illness history, past medical history, family history, allergy history, pertinent examination findings, comorbid conditions, and medication use. Additionally, we will meticulously document their prior clinical information from assisted reproductive technology (ART) treatments, including treatment protocols, cycle specifics, and outcomes.

### Outcome acquisition

We will obtain clinical outcomes, which include clinical pregnancy and embryo implantation at 28 days, as well as biochemical pregnancy at 14 days following embryo transfer.

### Data analysis

#### Data statistics

Data analysis was conducted using the SAS 9.4 statistical software (SAS Institute, Cary, NC, USA) by an independent statistician. Comparisons between the two groups will be performed as follows. For quantitative data, independent sample t-tests, analysis of variance, or Kruskal-Wallis H tests were employed; for categorical data, chi-square tests or Fisher’s exact probability method were utilized. All statistical analyses are two-sided, with *P* < 0.05 considered statistically significant.

#### Clinical prediction model

*Machine Learning Algorithm*. In this study, the SVC algorithm was selected for machine learning applications. All computations were executed using the Sklearn package within Python 3.10.

*Data Preprocessing*. Altogether four steps of data preprocessing were applied in this study. First, we will remove the outliers and organize the data. As for missing value filling, we will conduct KNN Imputer for continuous variables, and Simple Imputer for categorical variables. The Spearman correlation analysis was first conducted to evaluate the relationship between all predictive feature variables and clinical pregnancy outcomes (Spearman’s correlation coefficient more than 0.2 were significant). Eventually, we removed low-variance (Variance Threshold = 0.8) variables and highly correlated variables (r^2^>0.8).

*Prediction Variable Selection*. Thereafter, a SVC model was constructed using the remaining feature variables. The filtered feature subset was then input into the established model to rank the feature weights. These weights indicate the contribution of each feature to the determination of the SVC hyperplane. In accordance with the LIBSVM manual, SVC_coef was employed as the feature weight to compute the permutation importance of the features, with the feature exhibiting the maximum value of the mean ± standard deviation being deemed the most valuable predictive indicator.

*Model performance evaluation*. The dataset for the predictive model was partitioned into a training set and an internal validation set in a 7:3 ratio, with internal validation of the model conducted using cross-validation techniques. The accuracy of the classification results was assessed through the use of a confusion matrix. For binary classification tasks, sample cases can be categorized into four scenarios based on their actual class and the predicted class by the trained model: true positives (TP), false positives (FP), true negatives (TN), and false negatives (FN). The model’s accuracy was evaluated using the precision ratio (P) and recall rate (R). Ultimately, the F1 score was employed to synthesize both precision and recall. Additionally, the model’s performance was evaluated using the receiver operating characteristic (ROC) curve and the area under the curve (AUC).

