#### Sample size calculation

This study is a cross-sectional trial to establish a predictive model for endometrial receptivity and pregnancy outcomes using SVC to predict clinical pregnancy. The ultrasound assessments of uterine arteries and endometrial thickness are crucial for pre-implantation evaluation of endometrial receptivity, a study involving 78 FET patients (resulting in 45 clinical pregnancies, 57.7%) utilized elastic ultrasound imaging and nine predictive indicators based on basic information, achieving a predictive accuracy of 76.92% [15]. Sample size estimation was conducted using “pmsampsize” in R software [16]. According to the definition of RIF, at least two failed ETs were diagnosed as RIF. Assuming a clinical pregnancy rate of 30%, a minimum of 323 RIF patients were required for sample estimation. In a 1:1 ratio, 323 FI patients were also included. The code for sample size calculation is referenced in S1 Fig.

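### Outlier removal is the first modelling step and is not limited to recording errors, so genuine extreme blood-flow values can be lost from both training and validation data

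*Protocol article*

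**What the plan says.** The Data Preprocessing paragraph under Clinical prediction model announces its sequence with "Altogether four steps of data preprocessing were applied in this study". It begins with "First, we will remove the outliers and organize the data". For missing values, "we will conduct KNN Imputer for continuous variables, and Simple Imputer for categorical variables". Correlation screening against clinical pregnancy and removal of low-variance and collinear variables come next. Only in the later paragraph on model performance is it said that "The dataset for the predictive model was partitioned into a training set and an internal validation set in a 7:3 ratio".

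The Sample size calculation section states "Assuming a clinical pregnancy rate of 30%, a minimum of 323 RIF patients were required for sample estimation", obtained with the R package pmsampsize, and then "In a 1:1 ratio, 323 FI patients were also included". The Abstract gives the same two group sizes. The article states no allowance for exclusions.

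The Discussion makes the ultrasound blood-flow parameters the model's input features. It also says that studies of RIF point to abnormal flow.

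**The concern.** The article states an action here, namely removal, and puts no boundary on it. On its own rationale, unusual endometrial or uterine flow is where predictive information may lie. A step that takes out unusual values therefore acts directly on the predictors being tested.

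There are two readings of the step, and each has a cost:

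- **Patients are removed.** Precision, recall, F1 and AUC are then estimated only in women with no extreme value on any index, and the analysed number drops below the stated minimum.
- **Values are removed.** The number of patients is kept, but the imputation that follows fills the gaps with values typical of other patients. The tails of the Doppler and MV-FLOW measures are overwritten.

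Because the split is described after preprocessing, the validation data would be cleaned in the same way as the training data. A clinic applying the model could not set aside its atypical patients, so the reported performance would not be the performance met in use.

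**Working it through.** **1. The plan's own figure.** Inputs from Sample size calculation: pregnancy rate 0.30 and minimum 323. The margin is not stated; 0.05 is assumed as the package default.

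n = (1.96/0.05)² × 0.30 × 0.70 = 322.7, rounded up to 323. The stated figure is reproduced. Exactly 323 RIF patients are planned, so losing one leaves 322.

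**2. If whole patients are removed.** With an assumed share d lost, n = 323 × (1 − d), rounded down, and the half-width is 1.96 × √(0.21/n).

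| Share lost (assumed) | Patients left | Half-width on a 30% rate |
|---|---|---|
| 0% | 323 | 0.050 |
| 5% | 306 | 0.051 |
| 10% | 290 | 0.053 |
| 20% | 258 | 0.056 |

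If only values are removed and then imputed, n stays at 323.

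**3. How much an ordinary rule would flag.** The ultrasound section names 14 continuous indices: endometrial thickness, eight uterine artery measures (PSV, EDV, TAMV, TAPV, PGmean, S/D, RI, PI), VI^MV, EV, VI, FI and VFI. The article gives neither their distributions nor their correlations, so both are assumed. Simulation of 200,000 patients with equal pairwise correlation, 1.5-IQR rule:

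| Assumed shape | At least one flag, correlation 0.3 | At least one flag, correlation 0.6 | Single values flagged |
|---|---|---|---|
| Normal | 8% | 6% | 0.7% |
| Log-normal, log-SD 0.3 | 20% | 13% | about 2% |
| Log-normal, log-SD 0.5 | 31% | 20% | 3.8% |

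A 3-SD rule at correlation 0.3 flags at least one value in about 3.5%, 11% and 15% of patients. Under the log-normal shapes almost all flagged values are high; low values are practically never flagged.

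**4. Whether removal can be related to outcome.** One assumed log-normal predictor (log-SD 0.5 to 1.0), pregnancy rate 30%, AUC about 0.665 before trimming. The 1.5-IQR rule removes 4% to 8% of patients. The pregnancy rate is 56% to 60% among those removed and about 28% to 29% among those kept. AUC after trimming is 0.64 to 0.65. In this example trimming changes the outcome mix and lowers AUC. It shows that removal need not be neutral; it does not establish the direction in this study.

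**The case against.** The strongest reply is that this is one condensed sentence in a journal article. Removing outliers and organising data may mean ordinary cleaning of recording errors, with the rule held in the full protocol or analysis plan. Imputation follows directly, which fits deletion of single values rather than of patients. The order of description is also weak evidence of the order of execution: the paragraph mixes tenses, and it calls the correlation screening first although two steps precede it. The larger shares in the simulation need log-normal indices and modest correlation, yet several indices are functions of each other (S/D and RI both derive from PSV and EDV), and RI is bounded by 1 and cannot be log-normal. At correlation 0.8 the shares fall to about 4%, 9% and 14%.

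Much of this stands. The absence of a numerical outlier rule is not in itself the finding, and removal from the validation data is an inference from the described order. The reply does not dispose of the point, because the text prescribes removal without confining it to errors. If errors alone were meant, the sentence should say so.

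A reader might infer three stronger things that the article does not support:

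- That the analysed number necessarily falls short of 323. That follows only if whole patients are dropped.
- That trimming makes performance look better. The worked example moves AUC downwards.
- That low-flow and high-flow patients are lost alike. If the indices are right-skewed, the loss is mainly of high values.

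**Conclusion.** The point holds in a limited form. The plan states an unrestricted removal of outliers from the predictors under study and, as described, does so before the data are split. Genuine extremes can therefore be deleted or replaced by imputed values in both parts of the data, and performance would describe a trimmed population. The direction of the effect on AUC is uncertain.

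The possible extent is about 6% to 31% of patients with at least one flagged index, or 0.7% to 3.8% of single values. This rests on a 1.5-IQR rule, normal or log-normal shapes and correlations of 0.3 to 0.6, none of which the article gives. The effect on sample size is conditional and modest: at an assumed 10% loss of patients, the margin goes from an assumed 5.0 to 5.3 points. Selective trimming is the main problem, not the shortfall in number.

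**What to change.** Replace the outlier step with the following:

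- Set a value to missing only if it lies outside pre-specified physical limits or is confirmed as a recording error, judged without sight of the pregnancy outcome.
- Keep all other values, and all patients, in both the training and the validation data.
- Deal with skewness by log transformation or robust scaling. Fit these and the imputation in the training data only, then apply them unchanged to the validation data.
- Report one sensitivity analysis with extreme values winsorised.

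The cost is one reworded step and one extra model run, with no new data. Reported performance may change in either direction. If the intention was always to remove errors only, the change to the outlier step itself is a clarification.

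### As written, the outcome-based Spearman screen precedes the 7:3 split and is not confined to training patients; if it removes variables, the internally validated AUC is optimistic

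*Protocol article*

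**What the plan says.** The sub-section Clinical prediction model (under Data analysis) sets out its steps in this order.

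- **Data Preprocessing:** outliers are removed and missing values imputed. Then "The Spearman correlation analysis was first conducted to evaluate the relationship between all predictive feature variables and clinical pregnancy outcomes", with the rule that a Spearman "correlation coefficient more than 0.2 were significant". Low-variance and highly correlated variables are removed last.
- **Prediction Variable Selection:** "Thereafter, a SVC model was constructed using the remaining feature variables". Next, "The filtered feature subset was then input into the established model to rank the feature weights".
- **Model performance evaluation:** "The dataset for the predictive model was partitioned into a training set and an internal validation set in a 7:3 ratio". Cross-validation, of a type not specified, is named as the means of validating the model internally. Precision, recall, F1, ROC curve and AUC are the performance measures.

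No sentence limits the Spearman step to the training set or repeats it within cross-validation folds, and no external or separate test set is described. The Discussion says that every ultrasound-derived uterine blood-flow parameter will be entered as a feature.

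**The concern.** A screen against clinical pregnancy uses the outcome. Run on everyone before the split, it lets the pregnancies of the later validation patients influence which features enter the model. The hold-out set is then no longer independent of model building. Cross-validating the reduced feature set does not repair this, because the selection has already seen every fold.

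Internal validation is the only evidence of performance described for this single-centre study, so nothing later in the plan would expose the optimism. The bias is largest when the true signal is weak. The Discussion itself cites two studies that found no difference in endometrial flow indices between pregnant and non-pregnant women, alongside a meta-analysis that did find differences. A weak-signal result is therefore a realistic possibility.

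The cut is a second problem. A coefficient of 0.2 is labelled as significant, while the Data statistics sub-section sets two-sided P < 0.05. If 0.2 is a gate, it could discard a real but modest marker, including an MV-FLOW index, before any multivariable model is fitted.

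**Working it through.** **Inputs from the protocol article.** 323 RIF patients and a 30% clinical pregnancy rate; 323 FI patients at 1:1, total 646 (Sample size calculation). Cut 0.2 and split 7:3 (Clinical prediction model). Two-sided P < 0.05 (Data statistics).

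**Assumed, because not given.** 30 candidate features, independent and normally distributed; the cut applied to |rho|; 30% events also at n = 646.

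**1. The plan's own figure.** With a margin of 0.05 for the overall risk (assumed, the usual setting), n = (1.96/0.05)² × 0.30 × 0.70 = 1536.64 × 0.21 = 322.69, rounded up to 323. This matches the article. The figure does not depend on the present point; it supplies n and the event rate for the checks below.

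**2. What 0.2 means at n = 323.**
- 5% limit: 1.96/√322 = 0.109.
- P-value at 0.2: z = 0.2 × √322 = 3.59, two-sided p ≈ 0.0003.
- Chance that at least one pure-noise feature passes: 1 − (1 − 0.00033)^k, which is 0.8% for k = 25 and 1.3% for k = 40.
- Equivalent single-predictor AUC: rho = √(12 × 0.3 × 0.7) × (AUC − 0.5) = 1.587 × (AUC − 0.5). So rho 0.2 corresponds to 0.5 + 0.2/1.587 = 0.626.
- Survival of a real predictor with AUC 0.60: rho = 1.587 × 0.10 = 0.159. By Fisher z, (0.2027 − 0.1601) × √320 = 0.76, upper tail 0.22. It would be dropped about 78% of the time.

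**3. Effect of screening before the split.** Simulation with 2,000 to 6,000 data sets per scenario, a 7:3 split (226/97) and a ridge linear discriminant standing in for a linear SVC. AUCs are averages over data sets in which at least one feature passed. The true AUC is that of the same fitted model in new patients.

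| Informative features among 30 (n = 323) | Data sets with any selected | Hold-out AUC, screen on all | True AUC | Optimism | Hold-out AUC, screen in training only |
|---|---|---|---|---|---|
| none | 0.9% | 0.645 | 0.500 | 0.145 | 0.502 |
| 30 at rho 0.05 | 8.9% | 0.642 | 0.532 | 0.110 | 0.533 |
| 10 at rho 0.10 | 27.8% | 0.644 | 0.564 | 0.080 | 0.563 |
| 10 at rho 0.15 | 83.3% | 0.687 | 0.623 | 0.064 | 0.631 |
| 5 at rho 0.20 | 95.8% | 0.718 | 0.682 | 0.036 | 0.683 |
| 3 at rho 0.25 | 99.1% | 0.741 | 0.727 | 0.014 | 0.723 |

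At n = 646 the optimism for rho 0.05, 0.10, 0.15, 0.20 and 0.25 is 0.099, 0.071, 0.048, 0.024 and 0.006.

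**4. Does later cross-validation rescue it?** No. With n = 323 and all 30 features at a single-predictor AUC of 0.55, the pre-split screen gave hold-out AUC 0.649 and five-fold AUC 0.646 against a true 0.554. With ten features at 0.58 and 20 null, the figures were 0.662 and 0.663 against 0.594. Screening inside the training set gave 0.558 (true 0.561) and 0.599 (true 0.599).

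**5. Sensitivity.** An actual linear SVC gave the same picture in those two scenarios: 0.645 against 0.553, and 0.660 against 0.597. With single-predictor AUCs of 0.626 to 0.65 and feature correlation of 0 or 0.6, optimism was 0.02 to 0.04 at n = 323 and 0.002 to 0.033 at n = 646.

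**The case against.** The strongest reply is that the article never says which patients enter the screen. The partition appears under a topical heading in a condensed paper, and the ordering words link preprocessing to model fitting without placing the split. A reader might infer that the screen is definitely run on all patients and that the AUC is certainly inflated; the text implies this order but does not state it. What stands is that the written order puts the screen first and no sentence limits it to training data. That is a procedure as described, not a detail merely left to an analysis plan.

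The drop rule is also inferred. The only variables expressly removed are low-variance or highly correlated ones, and neither filter uses the outcome. The Discussion's intention to input all ultrasound blood-flow parameters fits a descriptive Spearman step. If 0.2 is only a label, this step selects nothing, and both the optimism and the 78% loss fall away. Against that, the SVC is fitted on remaining variables and a filtered subset. The two places need reconciling.

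The size is assumption-dependent. Independence is unrealistic for indices taken from the same waveform or the same 3D acquisition, and the weakest-signal figures are conditional on a feature passing, which is then uncommon.

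Two further readings are tempting but unsupported. One is that the rule discards every inversely related predictor: no sign is stated, and |rho| is the ordinary reading. The other is that the wave-motion classes ("positive wave, negative wave, quiescent wave, bidirectional wave, local peristaltic wave") are correlated through arbitrary code numbers: the article does not say how they are coded. Finally, 0.2 is stricter than P < 0.05, so calling it significant is loose wording that does not admit extra noise.

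**Conclusion.** The point holds conditionally. If the written order is followed and the screen removes variables, the internally validated AUC is biased upwards. The direction was the same in every scenario simulated, and the bias disappeared when the screen was confined to training data.

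The documents do not fix its size. Given 30 independent features and at least one selected, it is about 0.06 to 0.11 at n = 323 for rho 0.05 to 0.15, and 0.01 to 0.04 for rho 0.20 to 0.25. It is smaller for the same predictors at n = 646. It reaches 0.145 when pure noise passes, but that happens in only about 1% of data sets at n = 323. For strong predictors the effect is minor; for weak ones it could make a nearly uninformative model look useful.

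The arithmetic on the cut does not depend on the leakage question: 0.2 is not the 5% limit at n = 323. The loss of modest predictors follows only if 0.2 is a gate.

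**What to change.** - Split, or form the folds, first. Run imputation, any outcome-based screen (on |rho|), the variance and correlation filters and the importance ranking inside the training data only, refitted in every fold through one sklearn pipeline.
- State whether 0.2 removes variables or only describes them, and reconcile this with the Discussion.
- Call 0.2 a relevance cut rather than significant.

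Removing the screen altogether or forcing the MV-FLOW indices into the model would be modelling preferences; neither is needed to remove the bias.

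**Cost:** some rewording and slightly more code in software already planned, with no extra patients or data. The reported AUC will probably be lower. The screen will also be noisier on 226 training patients than on 323: the chance that at least one of 25 to 40 noise features passes rises from about 0.8–1.3% to about 6.5–10.2%. Correctly nested validation reflects this instead of hiding it.

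### As written, features are screened against clinical pregnancy before the 7:3 partition and nothing confines the screen to training patients, so the internal-validation AUC is likely to be optimistic

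*Protocol article*

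**What the plan says.** The section on the clinical prediction model in the protocol article sets out its steps under successive sub-headings.

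- **Data Preprocessing.** Outliers are removed. For missing values, "we will conduct KNN Imputer for continuous variables, and Simple Imputer for categorical variables". Next, "The Spearman correlation analysis was first conducted to evaluate the relationship between all predictive feature variables and clinical pregnancy outcomes", and the rule given is that a "correlation coefficient more than 0.2 were significant". Low-variance and highly inter-correlated variables are then removed.
- **Prediction Variable Selection.** "Thereafter, a SVC model was constructed using the remaining feature variables". Then "The filtered feature subset was then input into the established model to rank the feature weights", and the top-ranked feature is named the most valuable predictor.
- **Model performance evaluation.** The split is first mentioned here: "The dataset for the predictive model was partitioned into a training set and an internal validation set in a 7:3 ratio". How validation is done is covered by one further phrase, "with internal validation of the model conducted using cross-validation techniques". Precision, recall, F1, the ROC curve and AUC are reported.

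The sample size section supplies the scale: "Assuming a clinical pregnancy rate of 30%, a minimum of 323 RIF patients were required for sample estimation".

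**The concern.** A validation set is informative only if its outcomes played no part in building the model. Here the screen uses clinical pregnancy itself. If it is run on all patients, a feature that looks strong by chance in the later validation patients is more likely to be kept, and the same patients then confirm it. Cross-validation does not repair this if the folds are drawn after a pooled screen, because every fold inherits the selection.

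The stake is the study's first aim, the predictive precision of the MV-FLOW indices in patients with recurrent implantation failure (RIF). The only assessment described is internal and at one centre. The Discussion intends to name the most predictive indices and to argue for clinical use. Unlike sampling error, this bias favours the model on average.

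**Working it through.** **1. Order of the steps.** The text links them with sequence words (*first*, *Eventually*, *Thereafter*, *then*). The partition first appears after screening, filtering, fitting and ranking. Nothing says that any of these is repeated within the training part or within folds.

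**2. The plan's own figure.** Estimating an overall risk of 0.30 to within ±0.05 needs n = (1.96/0.05)² × 0.3 × 0.7 = 322.7, rounded up to 323. The stated number is reproduced and is not in dispute. It implies:

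- about 0.3 × 323 = 97 pregnancies;
- a 7:3 split into about 226 training and 97 validation patients;
- about 0.3 × 97 = 29 pregnancies in the validation set.

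**3. Why a 0.2 cut-off selects on chance.** For a feature with standardised difference d and event proportion p = 0.3, the correlation with the outcome is approximately r = d√(pq)/√(1 + d²pq), where q = 1 − p and √(pq) = 0.458. Its standard error near zero is about 1/√322 = 0.056.

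- d = 0.25: r = 0.1146/1.0065 ≈ 0.11. The feature passes only if chance adds about (0.20 − 0.114)/0.056 ≈ 1.5 standard errors. Some 97/323 = 30% of the patients supplying that chance are the validation patients.
- d = 0.7: r = 0.321/1.050 ≈ 0.31. The feature passes almost regardless, so selection carries little luck.
- Pure noise: 0.2/0.056 ≈ 3.6 standard errors, two-sided probability about 0.0003. With 30 features, 30 × 0.0003 ≈ 1%.

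**4. Size, by simulation.** The documents give n = 323, 30% events and the 7:3 split. The assumptions are 30 independent candidate features, the signal strengths below, and the 0.2 rule applied to the absolute coefficient. The screen uses all patients, a linear score is fitted in the training part, and its AUC in the validation part is compared with its AUC in new patients. Results are for runs in which at least one feature passed.

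| Informative features | Runs with a feature passing | Validation AUC | AUC in new patients | Optimism |
|---|---|---|---|---|
| 10 at d = 0.25 | about 43% | 0.650 | 0.576 | 0.074 |
| 10 at d = 0.30 | about 70% | 0.670 | 0.603 | 0.067 |
| 5 at d = 0.35 | about 68% | 0.669 | 0.616 | 0.053 |
| 3 at d = 0.50 | about 95% | 0.707 | 0.686 | 0.021 |
| 3 at d = 0.70 | not tabulated | 0.800 | 0.797 | 0.003 |

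When only training patients were screened, optimism was about zero (−0.003 to 0.008 across the linear-score and SVC runs without missing data). Outside the tabulated range, 8 features at d = 0.2 gave 0.087, but a feature passed in only 17% of runs.

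**5. Which step causes it.** A second version used a class-weighted linear SVC with an assumed 10% missing data and KNN imputation.

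| Scenario | Steps run on all patients | AUC optimism | F1 optimism |
|---|---|---|---|
| 8 at d = 0.3 | imputation and screen | 0.061 | 0.044 |
| 8 at d = 0.3 | imputation only | −0.004 | −0.012 |
| 8 at d = 0.3 | none | −0.007 | −0.017 |
| 3 at d = 0.5 | imputation and screen | 0.014 | 0.005 |
| 3 at d = 0.5 | imputation only | −0.018 | −0.020 |
| 3 at d = 0.5 | none | −0.017 | −0.023 |

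The small negative values fit a validation set that carries imputed values, compared with new patients who have complete data. Pooled imputation is indistinguishable from training-only imputation, so the outcome screen drives the inflation.

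**The case against.** **The order is inferred.** The article never says that the whole data set was used, or that the partition came afterwards. It is a condensed text with mixed tenses, and the Spearman step is described third although it is said to come first. Fold-level detail is often left to code or a fuller plan. This stands as a limit on certainty: a reader might infer that the protocol declares a pooled screen, and it does not. But the article is not silent on order. It gives a sequence, and that sequence, followed literally, biases the validation.

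**The filter is inferred.** The text calls coefficients above 0.2 significant. The only removals it states outright are for low variance and high inter-correlation, neither of which uses the outcome. If the 0.2 rule is only descriptive, the outcome leak into feature choice disappears and the in-sample ranking remains. Against this, the rule has a cut-off, sits among the preprocessing steps, and leads to features described as remaining and filtered. A filter is the natural reading, though not the only one.

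**The size depends on the scenario.** Feature count and signal strength are not in the documents. The largest optimism belongs to settings in which the screen often passes nothing, and strong predictors show almost none. This stands in full, and any figure should be quoted with its condition.

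**A model with no skill would not usually look useful.** A reader might infer that it would. At the plan's 0.2 cut-off, any of 30 noise features passes in only about 1% of studies, so usually there would be no model to report. That stronger reading is not supported.

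**Conclusion.** The point holds in a limited form. As written, outcome-based screening, filtering and ranking precede the partition and the cross-validation, and nothing confines them to training patients. If the 0.2 rule is a filter, the internal-validation AUC is optimistic by about 0.02 to 0.07 for weak to moderate signals (d from 0.25 to 0.5) and by nearly nothing at d = 0.7. These figures assume 323 RIF patients, 30% pregnant, about 30 candidate features and at least one feature passing.

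The in-sample ranking can separately bias which index is named most valuable. That matters for a study meant to judge MV-FLOW, but it was not quantified here.

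Two further inferences should be resisted. Imputing before the split is poor practice, but it added no measurable inflation. And F1 should not be called materially inflated, since its optimism against new patients was 0.00 to 0.04.

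**What to change.** State that the 7:3 partition, or each cross-validation fold, is made first. Fit imputation, the Spearman screen, the variance and correlation filters and the SVC in the training part only, as one pipeline re-run in every fold and applied unchanged to the held-out part. Compute permutation importance on held-out patients. State whether the 0.2 rule removes features or only describes them. If the authors already intend all this, a sentence saying so is enough.

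The cost is slightly more coding and a somewhat lower reported AUC. No extra patients or data are needed. One consequence to plan for is that a training part may pass no feature at 0.2 (26.5% of runs with 8 features at d = 0.3), so the text should say what is reported in that case.
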